### Perceptual assessments

Perceptual assessments of participants’ local thermal and comfort sensations will be assessed via Likert scales, to establish time-dependent changes in subjective perceptions of cooling [39]. The Likert scales for thermal sensation, thermal comfort, and thermal acceptance were created based on the recommendations of Schweiker et al. [40], i.e. using a ruler to draw a 100 mm horizonal line the anchors were then spaced evenly along the line. Thermal sensation consisted of a 7-point scale from 1 (cold) to 7 (hot) with 4 as neutral. Thermal comfort used a 5-point scale ranging from 1 (comfortable) to 5 (extremely uncomfortable) and thermal acceptance used a 4-point scale ranging from 1 (clearly acceptable) to 4 (clearly unacceptable). Perceptual sampling will occur at pre-determine time points throughout the entire pressure protocol (Fig 2). This evaluation will establish ageing- and SCI-induced changes in peripheral neurosensory function, as well as the relationship between the physiological and perceptual effects of cooling during mechanical loading.

### Statistical analyses

Data will be assessed for normality of distribution (Kolmogorov—Smirnov test), and then analysed for the independent and interactive effects of pressure stimuli’s temperature (i.e. 3 levels: 38, 24, 16 °C), and of participant group (i.e. 3 levels: young, older, SCI) on within- and between-subject mean differences in peak hyperaemia (N = 35 with 95% Confidence Intervals). This will be conducted using a 2-way mixed model ANOVA or Friedman, depending on the data distribution (parametric or non-parametric, respectively). Post-hoc analyses will be performed between pressure stimuli’s temperatures and participant groups based on the presence of main effects and using Tukey’s test. The use of regression models will evaluate the relationship between absolute cooling temperatures and peak hyperaemia during pressure stimuli. This approach is designed to identify “physiological thresholds” for the protective effects of cooling under mechanical loading. Mean thresholds will subsequently be determined and their inter-individual variability across the cohort. For the perceptual data, thermal discomfort will identify “Uncomfortable” on the Likert Scale as the threshold onset of discomfort. Regression analyses will be used to interrogate the relationship between pressure stimuli’s cooling temperature and local discomfort, for each participant. This approach will also enable the assessment of “perceptual cooling thresholds” for cold-induced discomfort at two absolute cold temperatures (i.e. 24 and 16 °C), and their individual variability. Physiological and perceptual thresholds will be combined to produce common cooling parameters that will accommodate different cooling characteristics. Regarding the secondary experimental outcomes, these will be within- and between-subject changes in biomarkers’ expression, skin structural and biophysical properties (i.e. imaging parameters and skin friction), and subjective thermal perceptions, as a function of pressure stimuli temperature (i.e. 3 levels: 38, 24, 16°C), time (i.e. varying levels depending on variables’ sampling rate), and of participant group (i.e. 3 levels: young, older, SCI). Data will be first assessed for normality of distribution (Kolmogorov—Smirnov test), and then analysed for the independent and interactive effects of pressure and stimuli temperature, time, and participant group by means of a 3- way mixed model ANOVA (or Friedman). Post-hoc analyses will be performed between pressure stimuli temperatures, time, and participant groups based the presence of main effects and using Tukey’s test. Group-related co-variables associated with sex, skin tone, and clinical status (applicable to SCI participants only, e.g. rehabilitation status) will be considered in all analyses to interpret the proportion of variance unexplained by the main effects (i.e. temperature, time, and group) and their interactions.

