## Abstract

This study protocol aims to investigate how localised cooling influences the skin’s microvascular, inflammatory, structural, and perceptual tolerance to sustained mechanical loading at the sacrum, evaluating factors such as morphology, physiology, and perceptual responses. The protocol will be tested on individuals of different age, sex, skin tone and clinical status, using a repeated-measure design with three participants cohorts: i) young healthy (n = 35); ii) older healthy (n = 35); iii) spinal cord injured (SCI, n = 35). Participants will complete three testing sessions during which their sacrum will be mechanically loaded (60 mmHg; 45 min) and unloaded (20 min) with a custom-built thermal probe, causing pressure-induced ischemia and post-occlusive reactive hyperaemia. Testing sessions will differ by the probe’s temperature, which will be set to either 38°C (no cooling), 24°C (mild cooling), or 16°C (strong cooling). We will measure skin blood flow (via Laser Doppler Flowmetry; 40 Hz); pro- and anti-inflammatory biomarkers in skin sebum (Sebutape); structural skin properties (Optical Coherence Tomography); and ratings of thermal sensation, comfort, and acceptance (Likert Scales); throughout the loading and unloading phases. Changes in post-occlusive reactive hyperaemia will be considered as the primary outcome and data will be analysed for the independent and interactive effects of stimuli’s temperature and of participant group on within- and between-subject mean differences (and 95% Confidence Intervals) in peak hyperaemia, by means of a 2-way mixed model ANOVA (or Friedman). Regression models will also be developed to assess the relationship between absolute cooling temperatures and peak hyperaemia. Secondary outcomes will be within- and between-subject mean changes in biomarkers’ expression, skin structural and perceptual responses. This analysis will help identifying physiological and perceptual thresholds for the protective effects of cooling from mechanically induced damage underlying the development of pressure ulcers in individuals varying in age and clinical status.

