This study protocol aims to investigate: 1) how different levels of localised cooling influences the skin’s microvascular, inflammatory, structural, and perceptual responses to sustained mechanical loading at the sacrum; and 2) how aging and spinal cord injury may modulate the metabolic, immunological, biophysical, and perceptual pathways underlying the beneficial effects of localised cooling on skin tolerance to mechanical loading. To achieve our aims, we have designed a clinically relevant experiment in healthy young participants and in groups at-risk of PUs (i.e., older and SCI), as detailed in the sections below. The investigation will offer a combination of skin viability, thermal physiology, and non-invasive skin sensing technologies, to develop new basic knowledge on the role of temperature in reducing the risk of skin damage. This will support innovation in the design of healthcare and user-centred technologies, such as mattresses, clothing, and medical devices that can safely interface with the skin and provide some protection from damage. This will unlock the potential of cooling to the skin that will help maintain skin health across the life course.

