### Participants

Three participant cohorts will be recruited: i) young healthy (n = 35); ii) older healthy (n = 35); and iii) spinal cord injured (SCI, n = 35). Sample size calculations were performed using Gpower (Gpower 3.1) with an effect size f = 0.4 for a repeated-measure ANOVA [parameters: within-between interaction; α = 0.05; β = 0.80; 3 groups; 3 measurements (i.e. peak hyperaemia at 38, 24, 16°C)], based on published data on the mean difference in peak hyperaemia (expressed as percentage of maximal cutaneous vascular conductance, CVCmax) during control conditions (32.7 ± 9.4% CVCmax) and during sensory nerve block (17.3 ± 6.8% CVCmax) [27]. Changes in peak hyperaemia were identified as the primary experimental outcome, as this represents a robust and repeatable microvascular response. The effects of cooling on peak hyperaemia are likely to be similar to those of cutaneous sensory nerve bloc [27], given that cooling also impairs the activity of cutaneous sensory nerves [28]. Hence, it was identified that the 50%-reduction in peak hyperaemia reported by Lorenzo and Minson [27] was a large (f = 0.4) and physiologically meaningful effect size to evaluate the beneficial effects of cooling on sustained mechanical loading. Based on the data above, we estimated a minimum sample size of 18 participants per group, and we propose testing of 35 individuals per group to allow for sufficient statistical power and to account for up to 50% dropout. Participants will be recruited according to the criteria in Table 1.

**Table 1 pone.0303342.t001:** Participant inclusion and exclusion criteria.

Inclusion	Exclusion
18–70 years old (young healthy 18–35 years old; older healthy 55–70 years old).	Young and older health groups only (does not apply to SCI group, see text below): suffering from cardiovascular, metabolic, and neurological disorders and/or comorbidities, e.g., hypertension, diabetes, chronic lung disease.
Male or female (minimum 17 for each sex).	Raynaud’s disease.
Skin tone dark, medium, or light (minimum 11 for each tone—assessed via the Fitzpatrick Scale [29]).	Suffering from skin conditions (e.g., eczema).
Healthy groups only: physically active (i.e., performing exercise 1 to 3 times a week).	Under drug therapy affecting thermoregulation (e.g. muscarinic antagonists).
SCI group only: presenting thoracic injury/paraplegia (i.e., injury level within T1-S1).	Smoker or Vaper.
SCI group only: >12 months post-injury and no history of PUs.	

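### If the normality check fails, the named Friedman fallback can still test temperature but not the group effect or the temperature-by-group interaction on which the study is sized

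*Protocol article*

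**What the plan says.** The Participants section fixes the endpoint: "Changes in peak hyperaemia were identified as the primary experimental outcome". It sizes the study "with an effect size f = 0.4 for a repeated-measure ANOVA", with the within-between interaction as the target effect, three groups and three measurements. The second aim in the Introduction is to learn "how aging and spinal cord injury may modulate the metabolic, immunological, biophysical, and perceptual pathways underlying the beneficial effects of localised cooling".

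The Statistical analyses section then sets out the primary analysis in three steps:

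- A gate: "Data will be assessed for normality of distribution (Kolmogorov—Smirnov test".
- The effects wanted. Peak hyperaemia is to be "analysed for the independent and interactive effects of pressure stimuli’s temperature (i.e. 3 levels: 38, 24, 16 °C), and of participant group", the latter also at three levels.
- The method: "This will be conducted using a 2-way mixed model ANOVA or Friedman, depending on the data distribution (parametric or non-parametric, respectively".

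The Abstract repeats the pair of methods: "by means of a 2-way mixed model ANOVA (or Friedman". For biomarkers, skin structure and ratings the same section names a "3- way mixed model ANOVA (or Friedman", with time as a third factor. It adds that covariables for sex, skin tone and clinical status will be considered in every analysis.

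**The concern.** The two methods are offered as parametric and non-parametric versions of one analysis, but they do not answer the same questions. The mixed ANOVA has a within-participant factor (temperature), a between-participant factor (group) and their interaction. Friedman has a single within-participant factor and no covariates.

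What is at stake is Aim 2. Whether age or spinal cord injury changes the response to cooling is the interaction, and that is the effect entered in the sample-size calculation. If the data go to Friedman, the plan as written has no test of it, no test of a group difference, and no place for the covariates it promises. The secondary branch loses more: a one-factor test cannot separate temperature from time either.

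**Working it through.** **1. The plan's figure nearby.** The article gives no number for this point. The related figure is the minimum of 18 per group. For the interaction, a common form of the noncentrality is λ = f²·N·m/(1 − ρ). Assuming ρ = 0.5 and sphericity (neither is stated), N = 18 in total gives λ = 0.16 × 18 × 3 / 0.5 = 17.28 on 4 and 30 degrees of freedom, and power 0.885. So 18 matches a total rather than a per-group number under those assumptions. Other settings gave 4 to 42 per group, and none gave 18. That is a separate matter and nothing below depends on it.

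**2. What Friedman uses.** With n participants and k = 3 temperatures, let R_j be the sum over participants of the within-participant ranks for temperature j. Then

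Q = [12 / (n·k·(k+1))] · Σ R_j² − 3n(k+1), on 2 degrees of freedom.

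For n = 3 × 35 = 105 this reduces to Q = Σ(R_j − 210)² / 105. Group does not appear. A constant added to all three readings of a participant leaves that participant's ranks unchanged, so any shift common to a group cancels, whatever the distribution.

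**3. Numerical check of that cancellation.** In one simulated data set, Q = 1.1619 and p = exp(−1.1619/2) = 0.559. After adding 0, 10 and 100 to the three groups, Q and p were identical.

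**4. What each test detects.** Simulation with 3,000 runs, 35 per group, α = 0.05. Normal data, within-participant correlation 0.5 and total SD 1 are assumed. Monte Carlo standard error near 5% is √(0.05 × 0.95 / 3000) = 0.4 percentage points.

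| True effect | Mixed ANOVA, matching term | Friedman over temperature |
|---|---|---|
| Group only, f = 0.4 | 0.993 | 0.051 |
| Crossover interaction, f = 0.4, no average temperature effect | 1.000 | 0.018 |
| Temperature only | 1.000 | 1.000 |
| Temperature effect present in young, absent in SCI | 1.000 (interaction) | 1.000 |

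The last row needs care. Friedman rejects there because temperature has an effect on average, so the result cannot be attributed to a difference between groups. At 18 per group Friedman gave 0.052, 0.017, 1.000 and 0.996 in the same order.

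**5. Does another part of the plan supply the missing test?**

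- Tukey's test is parametric and is applied only where a main effect is present.
- The regression on the primary outcome is described as cooling temperature against peak hyperaemia, with no group term.
- Friedman run separately in each group gives three tests of temperature. Comparing their p-values is not a test of interaction.
- No between-group rank test, transformation or rank-based factorial method is named.

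**6. How likely is the branch?** The article does not say whether normality is tested per cell, pooled or on residuals, nor how many failures trigger the switch. The range below is for n = 35 in each of nine cells, with assumed distributions, and combines several simulations.

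| Rule and version of the test | Normal | Log-normal, log-SD 0.3 | log-SD 0.5 |
|---|---|---|---|
| Any of nine cells, parameters estimated (Lilliefors) | 36–38% | 88–93% | >99% |
| Any of nine cells, uncorrected | about 0% | about 6% | 34–39% |
| Majority of cells, Lilliefors | 0% | 5–8% | 58–62% |

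The 37% for normal data is 1 − 0.95⁹ = 0.370, which treats the nine tests as independent although each participant contributes to three cells. The span runs from about 0% to above 99%, so the probability is unknown.

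**The case against.** The first-named analysis, the two-way mixed ANOVA, does test temperature, group and their interaction, so the gap is conditional on the normality check. That stands. So does the point that Friedman still tests temperature, so Aim 1 survives on that branch.

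A reader might infer that the trial's primary question would be left with no valid test. The article does not support that wording. It names a primary outcome and two aims, without ranking one aim as the primary question. Aim 2 is central because the sample size rests on the interaction, but the loss is confined to group, interaction and covariates.

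A reader might also infer that the data will probably end up on the Friedman branch, since percentage changes, cytokine levels and ratings are often skewed or discrete. Skew is plausible, but no trial data are shown and the decision rule is not given. The case does not need a probability.

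It could be said that a journal article leaves such detail to the full plan. That is fair for the version of the Kolmogorov-Smirnov test and for whether residuals are checked, and neither is pressed here. It does not cover the fallback itself, which the article names three times and which cannot deliver the effects listed in the same section.

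**Conclusion.** The concern holds in a conditional form. If the Kolmogorov-Smirnov check points to non-normal data, the stated rule leads to a test that cannot address the group effect, the temperature-by-group interaction or the covariates. This applies to the primary analysis and, with time added, to the secondary ones. The effect of temperature remains testable.

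On that branch the loss is complete for the group effect. The cancellation of group shifts in the ranks rests on no distributional assumption, and the simulated detection rate of 5.1% is the error rate of the test. For the interaction, Friedman has no term at all, and any rejection reflects the average temperature effect. The simulated ANOVA rates (99.3% and 100%) do rest on the assumed normality, correlation and f = 0.4, and serve only as a contrast. No figure can be put on the chance of reaching the branch.

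**What to change.** Replace the Friedman option, in the Abstract and in both places in the Statistical analyses section, with a fallback that keeps the same model terms:

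- Fit a linear mixed model with temperature, group and temperature × group, adding time and its interactions for the secondary outcomes, and a participant random effect. The sex, skin-tone and clinical covariates can enter this model.
- Keep the outcome defined under Skin blood flow, the percentage change from the session's own baseline, or use its log form. Since percentage change = 100 × (peak/baseline − 1), log(peak/baseline) = log(1 + percentage change/100), so the baseline normalisation is retained. Modelling log peak flow alone would drop it and change the endpoint.
- Judge fit on the model residuals. If they are poor, use a permutation, bootstrap or rank-based factorial test of the same terms.
- Analyse the thermal sensation, comfort and acceptance ratings, if scored as ordered categories, with an ordinal mixed model carrying the same terms.

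The cost is a change of analysis wording and slightly more analysis work. No new data are needed. Recruitment began in January 2024, so the change should be recorded before the outcome data are analysed.

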## Materials and methods

### Overview

Participants will attend the laboratory within the Clinical Academic Facility located at Southampton General Hospital (Southampton, UK), to complete three experimental sessions separated by a minimum of 24 hrs. During the sessions, participants’ skin over the sacrum will be mechanically loaded (60 mmHg; 45 min) and unloaded (minimum tare load: 17.5 mmHg; 20 min) with a custom-built thermal probe, to cause pressure-induced ischemia and post-occlusive hyperaemia. The study will be a randomised cross-over design, involving three probe temperatures, which will be set to either 38°C (no cooling), 24°C (mild cooling), or 16°C (strong cooling). An overview of the study design can be found in Fig 1.

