### Experimental procedures

Once screened and recruited, participants will be invited to their pseudo-randomly allocated experimental session [31]. They will come to the laboratory wearing comfortable, loose-fitting attire. Upon arrival, participants will be seated whilst they acclimatise to the ambient conditions of the laboratory (22–24 °C; 50% RH) before recording height and body mass (Model 874; Seca GmbH, Hamburg, Germany).

Following the pre-experimental checks, participants will lie down in the prone position on a hospital bed. Care will be taken to ensure that participants are as comfortable as possible by providing pillows as necessary to support the pelvic region and upper body, given the length of time (75 minutes) they will need to remain in this position. The addition of the pillows also serves to support the lumbar region by flattening the sacroiliac joint and reducing any pronounced lordosis of the spine while lying in a prone position.

First, structural, and functional imaging of the skin of the sacral skin using Optical Coherence Tomography (OCT) will be performed. This will be followed by sampling of skin sebum at the sacrum for subsequent biomarker analysis, using an established methodology involving a 2-minute application time and tweezer extraction to avoid cross-contamination [32]. The investigator will then place a custom-built thermal probe over the sacrum and load it with a weight (see below for details) to achieve pressure of 60 mmHg. The thermal probe consists of a water-perfused set of Peltier elements, which provide local temperature control for a 36-cm^2^ plate. An optic fibre is integrated in the plate, flush to its surface, which allows for the continuous monitoring of skin blood flow via Laser Doppler Flowmetry (LDF). The thermal probe is mounted on a frame with an integrated strain gauge to estimate the force applied to the stimulator. When applied to the skin, the integrated device allows for the manipulation of local skin temperature (range: 0°C to >50°C; variable temperature rates under PID control), applied pressure and the concurrent monitoring of blood flow.

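### The primary model for this three-session cross-over names no session term, and in its likely forms it would use only participants who complete all three sessions, despite a 50% dropout allowance

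*Protocol article*

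**What the plan says.** **Design.** The Overview states: "The study will be a randomised cross-over design, involving three probe temperatures". Participants attend "to complete three experimental sessions separated by a minimum of 24 hrs". On order, Experimental procedures says only that "participants will be invited to their pseudo-randomly allocated experimental session", with a reference for the method.

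**Sample size.** The Participants section gives a minimum of 18 per group from a repeated-measures ANOVA calculation. It raises this to 35 per group partly "to account for up to 50% dropout".

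**Model.** Statistical analyses takes temperature (three levels) and group (three levels) as the factors for peak hyperaemia and continues: "This will be conducted using a 2-way mixed model ANOVA", with Friedman as the alternative for non-normal data. The closing sentence of that section lists the effects in the models when it speaks of "the proportion of variance unexplained by the main effects (i.e. temperature, time, and group) and their interactions". Time belongs to the secondary three-way models and means sampling within a session. The further variables to be considered are "Group-related co-variables associated with sex, skin tone, and clinical status". Neither list contains session number, period or sequence. The article does not say what happens to a participant who misses a session.

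**The concern.** In a cross-over, each participant's three temperatures are measured on three occasions, so occasion is part of the design. Here the occasions may be only 24 hours apart, and each loads the same marked site for 45 minutes. Some change in response from the first to the third session is plausible, though the article gives no estimate of it.

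Two things are at stake. The first is precision. A method that needs all three temperatures from each person discards the sessions of anyone who stops early, and the plan allows for up to half doing so. The second is bias. If people are likelier to stop after the 16 °C session, those who remain have received 16 °C later, on average, than 38 °C. Any drift across sessions then enters the temperature contrast. The Introduction and Discussion both say that cold discomfort limits adherence, so this pattern of dropout is one the article itself gives reason to expect.

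**Working it through.** **1. The plan's own figures.** Inflating 18 for 50% dropout gives 18 / (1 − 0.5) = 36, against 35 planned. Conversely, 35 × 0.5 = 17.5 completers. So the allowance counts completers, which fits an analysis of completers. (The 18 per group was not itself reproduced. With correlation 0.5 and sphericity, which the article does not state, the inputs give 18 in total. That is a separate matter and nothing below depends on it.)

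**2. Sessions used.** Assume 50% completion with an equal risk h of stopping after session 1 and after session 2: (1 − h)² = 0.5, so h = 0.293.
- Sessions recorded per group: 35 × (1 + 0.707 + 0.5) = 77.2.
- Sessions from completers: 17.5 × 3 = 52.5, or 68%.

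**3. Bias from the uneven split of 35 alone.** 35 = 5 × 6 + 5, so at best one of the six orders is one short. If it is the order 16, 24, 38, the mean session number of 16 °C exceeds that of 38 °C by 2/35 = 0.057. With a drift of d SD per session the bias is 0.057d: 0.014 SD at d = 0.25 and 0.029 SD at d = 0.5.

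**4. Bias when dropout follows the cold session.** Assume the risk is 2h = 0.586 after 16 °C and h/2 = 0.146 after either other temperature. The chance of completing is:
- 16 °C in session 1 or 2: 0.414 × 0.854 = 0.354
- 16 °C in session 3: 0.854² = 0.729

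The session number of 16 °C minus that of 38 °C averages −1.5, 0 and +1.5 when 16 °C comes first, second and third. With the six orders equally frequent, the mean among completers is 1.5 × (0.729 − 0.354) / (0.354 + 0.354 + 0.729) = 0.39 sessions. Bias = 0.39d: 0.10 SD at d = 0.25 and 0.20 SD at d = 0.5.

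**5. Simulation.** One group of 35, orders as equal as 35 allows, correlation 0.5, true contrast zero, 1,500 runs. Entries are the mean error of the 16 minus 38 °C contrast, with its SD in brackets, in units of the SD of peak hyperaemia at one temperature. The all-session fits used a random intercept with known variances.

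| d per session | Dropout | Completers only | All sessions, no session term | All sessions, session term |
|---|---|---|---|---|
| 0 | unrelated | −0.010 (0.244) | −0.004 (0.207) | −0.005 (0.209) |
| 0.25 | unrelated | 0.023 (0.255) | 0.016 (0.219) | 0.002 (0.220) |
| 0.5 | unrelated | 0.031 (0.271) | 0.025 (0.220) | 0.001 (0.209) |
| 0.25 | after 16 °C | 0.111 (0.251) | 0.099 (0.211) | −0.003 (0.213) |
| 0.5 | after 16 °C | 0.222 (0.282) | 0.197 (0.227) | −0.006 (0.215) |

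The completers-only entries in the last two rows exceed step 4 by about the amount in step 3. A second simulation under similar assumptions gave 0.08 to 0.19 SD without a session term when dropout followed the cold session, and up to about 0.03 to 0.06 SD when it did not.

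**6. Variance ratio, completers only against all sessions with a session term.** With no drift: 0.244² / 0.209² = 1.36. With d = 0.5 and dropout after 16 °C: 0.282² / 0.215² = 1.72. Across both simulations the range is about 1.2 to 1.7.

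**7. Choice of covariance.** A further run let the cooling effect vary between people (SD 50% of a true −15.4) and let dropout depend on the last response. An unstructured covariance gave −15.2 to −15.6. A random intercept alone gave −14.4 to −14.5, about 6% short. This serves only to choose the covariance structure; both the scale and the dropout rule were invented for the run.

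**The case against.** The strongest objection is that the article never says incomplete participants are dropped. A reader might infer that every participant who misses a session is discarded, but the text does not support that as a fact. The words mixed model ANOVA could mean a likelihood-based mixed model that keeps partial data, and rules for missing sessions may sit in an analysis plan that is not shown. This stands for the ANOVA branch. There, completers-only is the likely reading, because the sizing uses a repeated-measures ANOVA with a completer allowance, but it is not certain. It does not stand for Friedman, which needs a value in all three conditions. Nor does it touch the session term: the article lists its effects and session is not among them, and the table shows much the same bias with all sessions kept.

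Secondly, order is randomised, so a reader who infers that order effects generally sit in the temperature contrast goes too far. With dropout unrelated to temperature the bias is small, and that 35 is not a multiple of six hardly matters. This stands.

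Thirdly, peak hyperaemia is expressed relative to a same-session baseline at 34 °C. That removes proportional shifts in flow between sessions, but not a change in the hyperaemic response itself.

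Fourthly, dropout after the cold session is an assumption, and 50% is a ceiling rather than a forecast. The pattern may be weaker in the spinal cord injury group, where sensation below the injury may be lost. This stands as a limit on the size.

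**Conclusion.** The point holds as a weakness in the stated model, not as a demonstrated error in the result. The precision loss depends on completion: at 50% and on a completers-only analysis, about a third of recorded sessions go unused and the contrast variance is roughly 1.2 to 1.7 times larger. The bias of 0.1 to 0.2 SD needs two conditions together, dropout concentrated after 16 °C and a drift of 0.25 to 0.5 SD per session. Without the first it is at most about 0.03 to 0.06 SD in the cases tried; without the second it is about zero.

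Two further inferences are not supported. One is that the trial would be underpowered: the planned 35 already absorbs the loss, leaving 17.5 completers against the stated minimum of 18. The other is a specific percentage attenuation of the cooling effect. That would need dropout driven by the blood-flow response, for which the article gives no basis, and it would borrow the 32.7 − 17.3 = 15.4 point difference in % CVCmax from the sample size section, whereas the endpoint is percentage change from baseline.

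**What to change.** Make the primary analysis a linear mixed model fitted by REML to all attended sessions:
- fixed effects for temperature, group, temperature × group and session number (1 to 3);
- an unstructured within-participant covariance across the three temperatures or, if that does not converge, a random intercept with a random linear temperature effect;
- Kenward-Roger degrees of freedom.

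This should replace both the ANOVA and the Friedman branch. If residuals are skewed, transform the outcome within the same model. Keep the complete-case ANOVA as a sensitivity analysis. For participants still to be enrolled, allocate the six temperature orders in blocks within each group, if this is not already done.

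The cost is a change of wording before analysis, two degrees of freedom for session and a few covariance parameters. No extra participants or visits are needed. A session term does not remove carry-over from one session to the next, so that remains a separate assumption.
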